## Methods

### Design

A three-armed randomised controlled trial (RCT) will be conducted to compare minimal guided and unguided iSMI (GET.ON Stress) with a waiting list control condition (WLC). All intervention arms will have full access to treatment as usual (TAU). To control for potential confounding effects, TAU will be monitored. Assessments will take place at baseline (T1), post-treatment (7 weeks, T2), and at 6-months follow-up (T3; see Figure 
1 for a detailed overview of assessments). All procedures involved in the study will be consistent with the generally accepted standards of ethical practice. The study was approved by the University of Marburg ethics committee (No. 2014-5K). The trial is registered in the German clinical trials register under DRKS00005687.

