**Table 2 Tab2:** **Measures**

	T0	T1	T2	T3
Perceived stress scale	✓	✓	✓	✓
Center for epidemiological studies depression scale	-	✓	✓	✓
Maslach burnout inventory – emotional exhaustion	-	✓	✓	✓
Emotion regulation skills questionnaire – general distress	-	✓	-	-
Utrecht work engagement scale	-	✓	✓	✓
Trimbos/iMTA questionnaire for costs associated with psychiatric illness	-	✓	-	✓
EuroQol, SF-12 quality of life	-	✓	-	✓
Other measurements				
Demographic variables questionnaire	✓	-	-	-
Effort reward imbalance questionnaire – short form	-	✓	✓	✓
Client satisfactory questionnaire	-	-	✓	-
Potential dropout reasons	-	-	✓	-
Big five inventory – short form	-	✓	-	-
Volitional components questionnaire – short form	-	✓	-	-
General self-efficacy scale	-	✓	-	-
Self-regulation scale	-	✓	-	-
Self-control scale	-	✓	-	-
Psychotherapy motivation questionnaire – short form	-	✓	-	-
HAPA-questionnaire	-	✓	-	-
Internet affinity questionnaire	-	✓	-	-
Work limitations questionnaire	-	✓	✓	✓
The single-item presenteeism question	-	✓	✓	✓
A single item question on work ability	-	✓	✓	✓
Connor-Davidson resilience scale	-	✓	✓	✓

Note. T0 = Screening, T1 = Baseline, T2 = 7 weeks, T3 = 6 months.

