### Sample size calculation

We aim to include 408 participants. The study was designed based on the expected superiority of the active groups (minimal guided and unguided internet-based self-help) compared to the waiting-list control group on the primary outcome variable (i.e. perceived stress) at post-test. Based on pilot-evaluation data we expect a mean effect for the minimal guided treatment arm compared to the waiting list control group of d = 0.70. However, unguided internet-based interventions consistently produce lower effect sizes as guided interventions
[15] and a meta-analysis on traditional face-to-face interventions for work-related stress
[6] yielded an overall combined effect size of only d = 0.34. As we also want to examine the difference in the effectiveness of minimal guided and the unguided iSMI we aim to be able to detect difference between groups with an effect size of d = 0.30. Thus we need to include 408 participants. This sample will allow us to detect a between-group effect size (ES) of d = 0.30 with a power (1-ß) of 80 % and an alpha of .05 (calculated using PASS 12) in a one-tailed test (for uni-directional hypotheses H1: WLC < unguided < minimal guided iSMI).

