#### Cost-effectiveness and cost-utility analyses

In the cost-effectiveness analyses, treatment response (reliable positive change) will be the primary outcome, whereas quality adjusted life years (QALYs) will be the outcome in the cost-utility analyses. A cost-effectiveness acceptability curve
[72] will be calculated, when better outcomes are associated with higher costs. Such an acceptability curve represents the probability that the intervention is cost-effective relative to the control group, given varying thresholds for the willingness to pay (WTP) for gaining one additional treatment responder or gaining one additional QALY. Nonparametric bootstrapping will be applied to estimate confidence intervals for mean differences in costs and effects between groups.

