#### Incremental net-benefit regression analysis

Effect modification can be studied in the context of a health-economic evaluation to address the question if there are any baseline factors (i.e. subgroups of employees) associated with particularly favourable cost-effectiveness when the experimental intervention is offered. The data analytic approach taken here consists of incremental net-benefit regression analysis (INBRA). First, incremental net-benefits, Δ(NB), are calculated as *Δ*(NB) = WTP × *Δ*(QALY) - *Δ*(Costs), where WTP × Δ(QALY) is the willingness to pay for gaining one QALY and Δ(Costs) are the extra costs owing to offering the intervention. Δ(NB)s are calculated for each participant in the dataset and can then be analysed in a regression framework. In its simplest form the incremental net-benefits are regressed on the treatment indicator variable to evaluate the cost-effectiveness of the intervention relative to the control condition. When Δ(NB) exceeds €0, then the intervention is deemed to be cost-effective. The regression models can be expanded to include interaction terms of the treatment indicator variable and putative effect modifiers
[74, 75].

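### The cost-utility and net-benefit analyses, as described, name no adjustment for baseline EQ-5D utility or baseline costs, although both are collected before randomisation; chance imbalance therefore enters the QALY and cost differences and costs precision

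*Protocol article*

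**What the plan says.** In the Protocol article, the section on cost-effectiveness and cost-utility analyses makes treatment response the outcome for cost-effectiveness and QALYs the outcome for cost-utility. It then states: "Nonparametric bootstrapping will be applied to estimate confidence intervals for mean differences in costs and effects between groups". No covariate is named.

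The section on incremental net-benefit regression gives a model, its purpose and its extension: "In its simplest form the incremental net-benefits are regressed on the treatment indicator variable to evaluate the cost-effectiveness of the intervention relative to the control". The one extension mentioned is interactions between treatment and possible effect modifiers.

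Table 2 lists "EuroQol, SF-12 quality of life" and "Trimbos/iMTA questionnaire for costs associated with psychiatric illness", each ticked at T1 and T3 only. The eligibility and randomisation section requires the baseline assessment to be complete before allocation, so both T1 measures are pre-randomisation variables. The article does not give the QALY formula, the utility SDs or the correlation between baseline and 6-month values.

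**The concern.** Someone following the text would compare arm means of QALYs and costs, and would regress net benefit on arm alone. That leaves unused the two baseline variables most directly related to these outcomes.

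For QALYs there is a further reason to adjust. With utilities at two time points only, the usual straight-line calculation makes the baseline value half of the score. A chance difference between arms in pre-randomisation utility then enters the QALY difference twice: directly through the baseline term, and again through its correlation with the 6-month value. Bootstrapping reflects this variability in the interval but does not reduce it.

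Aims 3, 4 and 7 draw on these economic comparisons. The trial was sized for perceived stress, so nothing else in the design secures precision for QALYs or costs.

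**Working it through.** **Sample size.** The article gives no precision figure for the economic analyses, so the only figure to reproduce is the sample size. It states: "We aim to include 408 participants", to "detect a between-group effect size (ES) of d = 0.30 with a power (1-ß) of 80 % and an alpha of .05", "in a one-tailed test".
- n per arm = 2(1.645 + 0.842)² / 0.30² = 137.4, rounded up to 138. Three arms give 414, within 1.5% of 408.
- 408 / 3 = 136 per arm, if allocation is equal (the ratio is not stated). Power at 136 is Φ(0.30 / √(2/136) − 1.645) = Φ(0.829) = 79.6%.

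The stated size is reproduced, and 136 per arm is used below.

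**Assumptions (not in the document).** u0 and u1 are utility at T1 and T3, ρ is their correlation, and k = SD(u1) / SD(u0). The QALY over half a year is the straight-line area, 0.25(u0 + u1). Data are complete.

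**Share of QALY variance removed by adjusting for u0.** In units of 0.0625 × SD(u0)²:
- total variance = 1 + k² + 2ρk
- part explained by u0 = (1 + ρk)²
- share removed = (1 + ρk)² / (1 + k² + 2ρk), which is (1 + ρ)/2 when k = 1

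| k | ρ = 0 | ρ = 0.3 | ρ = 0.5 | ρ = 0.7 |
|---|---|---|---|---|
| 0.75 | 64% | 75% | 82% | 89% |
| 1 | 50% | 65% | 75% | 85% |
| 1.25 | 39% | 57% | 69% | 82% |
| 1.5 | 31% | 51% | 64% | 79% |
| 2 | 20% | 41% | 57% | 74% |

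Simulation with 136 per arm and k = 1 (4,000 runs) gave 65%, 74% and 85% at ρ = 0.3, 0.5 and 0.7. The share reaches one half only if ρ is at least 0 (k = 1), 0.18 (k = 1.25), 0.29 (k = 1.5) or 0.41 (k = 2). At k = 1.5 and ρ = 0.2 it is 44%.

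**Worked example on the utility scale.** Assume SD 0.20 at both times and ρ = 0.5.
- SE of the baseline utility difference = 0.20 × √(2/136) = 0.0243
- Shift in the unadjusted QALY difference from a one-SE baseline imbalance: 0.25 × 0.0243 = 0.0061 directly, and 0.25 × 1.5 × 0.0243 = 0.0091 with carry-over to T3
- Unadjusted SE = 0.25 × √(2 × 1.5) × 0.0243 = 0.0105
- Adjusted SE = 0.25 × √(1 − 0.25) × 0.0243 = 0.0053

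An ordinary chance imbalance thus moves the unadjusted estimate by 0.0091 / 0.0105 = 0.87 of its own SE, and adjustment halves the SE. Across SDs of 0.10 to 0.25 and ρ of 0.3 to 0.7, the unadjusted SE is 0.005 to 0.014 and the adjusted SE 0.002 to 0.007.

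**Other QALY definitions (k = 1).**
- T3 utility only: share ρ², or 9%, 25% and 49% at ρ = 0.3, 0.5 and 0.7.
- Change from baseline: share (1 − ρ)/2, or 35%, 25% and 15%.

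**Costs.** Baseline cost is not part of the follow-up cost, so the share is ρ² with ρ the baseline-to-follow-up cost correlation: 9% to 49% for ρ = 0.3 to 0.7.

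**The case against.** The strongest reply is that the article is silent, not wrong. It never calls the differences raw or unadjusted. A regression-adjusted difference is also a mean difference and can be bootstrapped. The indicator-only model is labelled the simplest form, and the text allows expansion. A condensed article may also leave covariates and the QALY formula to the full plan. This stands in part: a reader might infer that the plan excludes baseline adjustment, and the document does not support that. What remains is that the section describes a specific model and one specific type of extension, and baseline utility and cost appear in neither.

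A reader might also infer that at least half of the QALY variance is always avoidable. That requires the area-under-the-curve formula and roughly equal SDs, and the working shows cases where it fails. The net-benefit section speaks of QALY differences calculated for each participant. If that meant change from baseline, the gain would be only 15-35% at ρ = 0.3 to 0.7.

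Randomisation keeps the unadjusted difference unbiased in expectation, and the bootstrap interval allows for baseline variation. The analysis is therefore less precise, not invalid.

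It would also be tempting to express the loss as power. The Discussion says that health-economic evaluations do not test hypotheses, and the d of 0.30 was set for perceived stress, so it has no support as a utility effect. Imprecision still matters for a probabilistic decision, which rests on the estimate and its spread.

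**Conclusion.** The point holds in limited form. The economic estimators, as described, do not name adjustment for baseline EQ-5D utility or baseline costs, although both are available. The consequence is avoidable imprecision and exposure to chance imbalance, not expected bias.

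For an area-under-the-curve QALY, adjustment would remove 50-85% of the variance with equal SDs and ρ from 0 to 0.7, and 41-85% with k from 1 to 2 and ρ from 0.3 to 0.7. Over the full grid shown, the share runs from 20% (k = 2, ρ = 0) to 89% (k = 0.75, ρ = 0.7). Gains are smaller under the other two definitions, and equal ρ² for costs. All of these rest on an assumed QALY formula, assumed SD ratios and assumed correlations.

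Two extensions are not supported. The QALY figures do not carry over to net benefit, which also depends on cost variance, the cost correlations and willingness to pay, none of which is given. Nor does the QALY argument reach the response outcome of the cost-effectiveness analysis, which is based on the reliable change index; there, only the cost side is affected.

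**What to change.** In the section on cost-effectiveness and cost-utility analyses, state that QALY and cost differences are estimated by regression within each bootstrap replicate, for example by seemingly unrelated regressions on arm. Use baseline EQ-5D utility as covariate for QALYs and baseline TiC-P costs as covariate for costs.

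In the net-benefit section, include both baseline variables as main effects in every model, including the simplest one. Build the ICERs and acceptability curves from the adjusted differences, and report the unadjusted differences as a sensitivity analysis. Give the QALY formula in the same place, since the size of the gain depends on it.

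If the full plan already specifies this adjustment, one sentence saying so is enough. Otherwise it should be fixed before outcome data are seen, so that the choice cannot follow the results. The cost is a few lines of text and code; no extra data, visits or participants are needed.

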#### Cost-benefit analysis from the employer’s perspective

As indicated, a cost-benefit analysis will be conducted from the employer’s perspective. Costs, C, will be equated with intervention costs; benefits, B, with greater productivity owing to lesser absenteeism and lesser presenteeism. The ratio C/B is the cost-benefit ratio, and its inverse, B/C equals the return-on-investment, while the net-benefit is defined as B-C, which is the payout of offering the intervention. All health-economic evaluations will be conducted in accordance with the CHEERS statement for reporting health economic studies
[73]. Sensitivity analyses directed at uncertainty in the main cost-drivers will be conducted to ascertain the robustness of the outcomes.

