### Aims

Thus, this study aims at strengthening the evidence-base for internet- and mobile-based SMI (iSMI) by investigating the acceptability and (cost-) effectiveness of minimal guided and unguided iSMI in employees with heightened levels of perceived stress.

The study has the following specific aims: (1) To assess the effectiveness of minimal guided and unguided versions of iSMI for reducing perceived stress when compared to a waiting list control group (WLC). (2) To assess the comparative effectiveness of minimal guided and unguided iSMI. (3) To assess the cost-effectiveness of minimal guided and unguided iSMI compared to WLC. (4) To assess the comparative cost-effectiveness of minimal guided and unguided iSMI from a societal perspective. (5) To assess the cost to benefit ratio and return-on-investment of offering the interventions from an employer’s perspective. (6) To assess and compare acceptability of minimal guided and unguided iSMI. (7) To investigate in explorative analyses if there are any baseline factors (i.e. subgroups of employees) associated with particularly favourable cost-effectiveness when the experimental intervention is offered.

We hypothesise minimal guided and unguided iSMI both to be more effective and cost-effective than WLC; minimal guided iSMI to show higher effectiveness, cost-effectiveness and acceptability than unguided iSMI. Likewise, we expect guided iSMI to represent a better business case as seen from an employer’s perspective than unguided iSMI and WLC, respectively.

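### The employer analysis labels B/C, a benefit-cost ratio with break-even at 1, as the return-on-investment; it lies exactly 1 above the net return (B − C)/C

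*Protocol article*

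**What the plan says.** The section of the protocol article on the cost-benefit analysis from the employer's perspective defines five quantities.

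- Cost: "Costs, C, will be equated with intervention costs".
- Benefit: "benefits, B, with greater productivity owing to lesser absenteeism and lesser presenteeism".
- The two ratios: "The ratio C/B is the cost-benefit ratio, and its inverse, B/C equals the return-on-investment".
- The difference: "the net-benefit is defined as B-C, which is the payout of offering the intervention".

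The Aims section makes two of these a specific aim, the fifth: "To assess the cost to benefit ratio and return-on-investment of offering the interventions from an employer’s perspective". Net-benefit is not named in that aim. The hypotheses that follow expect the guided version to be a better business case for the employer than the unguided version and the waiting list.

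The article gives no amounts for B or C, no break-even value for the return-on-investment, and no statement of whether it will be shown as a ratio or a percentage.

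**The concern.** A return on an investment is ordinarily the net gain divided by the outlay. The article has the net gain, B − C, but does not use it in the return. It divides the gross benefit by the cost, and that quotient is the benefit-cost ratio.

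Two things follow. First, the quantity called a return is positive whenever B is positive, including when the employer gets back less than was spent. Second, the two measures named in aim 5 are reciprocals of each other, so they carry the same information, and neither turns negative merely because the cost is not recovered.

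At stake is how an employer reads the result. The business-case hypothesis against the waiting list turns on whether the benefit exceeds the cost, and a figure labelled as a return invites a comparison with zero. Elsewhere the article does use zero as a threshold: the section on incremental net-benefit regression calls the intervention cost-effective when the incremental net-benefit exceeds €0. That threshold is right for a difference such as B − C, but not for B/C.

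**Working it through.** **Inputs, all from the employer cost-benefit section.** C = intervention costs. B = productivity gain from less absenteeism and presenteeism. Stated cost-benefit ratio = C/B. Stated return-on-investment = B/C. Stated net-benefit = B − C. The article prints no numerical result on this point, so there is no figure to reproduce.

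**Step 1: is B gross or net?** B is defined by productivity alone, and C is subtracted from it afterwards to give the net-benefit. If B were already net of C, then B − C would deduct the cost twice. B is therefore gross, and the label cannot be rescued by reading it as net.

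**Step 2: the gap.**

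(B − C)/C = B/C − 1, so B/C − (B − C)/C = 1 for every C > 0.

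The gap depends on neither B nor C. Expressed as a percentage it is 100 percentage points.

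**Step 3: illustration.** C = 100 is assumed only to show the pattern.

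| B | C/B | B/C (stated return) | (B − C)/C (net return) | B − C |
|---|---|---|---|---|
| −50 | −2.0 | −0.5 | −1.5 | −150 |
| 0 | undefined | 0 | −1.0 | −100 |
| 50 | 2.0 | 0.5 | −0.5 | −50 |
| 80 | 1.25 | 0.8 | −0.2 | −20 |
| 100 | 1.0 | 1.0 | 0 | 0 |
| 150 | 0.667 | 1.5 | 0.5 | 50 |
| 200 | 0.5 | 2.0 | 1.0 | 100 |
| 300 | 0.333 | 3.0 | 2.0 | 200 |

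**Step 4: where the sign disagrees.** B/C > 0 while (B − C)/C < 0 exactly when 0 < B < C; the rows B = 50 and B = 80 are examples. At B = 0 or below, the stated return is not positive either. Above B = C both are positive, and the stated one is larger by 1.

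**Step 5: ranking of the arms.** Write r₁ and r₂ for B/C in the two active arms. The net returns are r₁ − 1 and r₂ − 1, so r₁ > r₂ if and only if r₁ − 1 > r₂ − 1. The order of the arms on this measure is the same under either definition, and so is the difference between them.

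**The case against.** The best defence is that nothing is miscalculated. The article prints its formula and says that it is the inverse of C/B, so it can be read as money returned per unit of money spent, with break-even at 1. Read that way, 0.8 back for every 1 spent is plainly a loss. For 0 < B < C, all three planned quantities show it: C/B is above 1, B/C is below 1 and B − C is negative. The formula (B − C)/C comes from general usage and stands nowhere in the article.

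Much of this stands, and it rules out several stronger readings that a reader might infer.

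- That the plan makes a loss look like a gain. This needs 0 < B < C and a reader who assumes break-even at 0. The net-benefit defined in the same sentence still shows the loss.
- That the plan will print inflated percentages. The article never says that the return will be given as a percentage. It is a protocol, so no return has been reported.
- That the return is the main result of aim 5. The aim names it alongside the cost to benefit ratio, and nothing ranks one above the other.
- That the guided-versus-unguided conclusion could reverse. A constant shift cannot change that order.

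What does not fall away is the label. The article calls a gross ratio a return without saying that it breaks even at 1, although it defines the net gain in the same sentence. Because the formula is stated outright, this is not a detail left to a fuller document.

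**Conclusion.** The point holds as a mislabelled measure. As defined, the return-on-investment is the benefit-cost ratio and lies exactly 1 above the net return for any positive cost. The size follows by algebra and needs no assumption about the data. That the gap matters rests on one assumption: that a return will be read in the usual net sense, with break-even at 0.

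Severity is minor to moderate and limited to aim 5. Data collection, the estimates of B and C, the net-benefit, the order of the active arms on this measure and the clinical outcomes are all unaffected. It should be corrected before reporting, because the discrepancy favours the intervention and the measure is named in a specific aim.

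**What to change.** In the employer cost-benefit section, replace the definitions of the ratios with:

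- net-benefit = B − C (break-even 0);
- benefit-cost ratio = B/C (break-even 1);
- return-on-investment = (B − C)/C (break-even 0).

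C/B can stay as the cost-benefit ratio. Aim 5 needs no rewording, since its two measures would then no longer be simple reciprocals.

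The cost is one line of text, with no new data and no change of design. The only downside for the authors is a reported return that is lower by 1.

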#### Incremental net-benefit regression analysis

Effect modification can be studied in the context of a health-economic evaluation to address the question if there are any baseline factors (i.e. subgroups of employees) associated with particularly favourable cost-effectiveness when the experimental intervention is offered. The data analytic approach taken here consists of incremental net-benefit regression analysis (INBRA). First, incremental net-benefits, Δ(NB), are calculated as *Δ*(NB) = WTP × *Δ*(QALY) - *Δ*(Costs), where WTP × Δ(QALY) is the willingness to pay for gaining one QALY and Δ(Costs) are the extra costs owing to offering the intervention. Δ(NB)s are calculated for each participant in the dataset and can then be analysed in a regression framework. In its simplest form the incremental net-benefits are regressed on the treatment indicator variable to evaluate the cost-effectiveness of the intervention relative to the control condition. When Δ(NB) exceeds €0, then the intervention is deemed to be cost-effective. The regression models can be expanded to include interaction terms of the treatment indicator variable and putative effect modifiers
[74, 75].

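### One symbol, Δ(NB), stands for both a participant-level outcome and the between-arm increment, so the > €0 rule for cost-effectiveness can be read on the wrong quantity

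*Protocol article*

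**What the plan says.** The protocol article, section Incremental net-benefit regression analysis, makes these statements in sequence:

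- Definition: Δ(NB) = WTP × Δ(QALY) − Δ(Costs). The cost term is defined as a between-arm quantity: these "are the extra costs owing to offering the intervention".
- Effect term: of the product of WTP and Δ(QALY), the article says that it "is the willingness to pay for gaining one QALY".
- Unit of calculation: the incremental values, it says, "are calculated for each participant in the dataset and can then be analysed in a regression framework".
- Model: the basic regression is set out next, with treatment as the only regressor: "In its simplest form the incremental net-benefits are regressed on the treatment indicator variable". Its stated purpose is "to evaluate the cost-effectiveness of the intervention relative to the control condition".
- Decision rule: the verdict depends on the sign of the same symbol. If it "exceeds €0, then the intervention is deemed to be cost-effective".
- Extension: interaction terms between treatment and candidate modifiers may be added.

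The Aims (aim 7), Primary and secondary outcomes and the Discussion call the subgroup question exploratory. The section Cost-effectiveness and cost-utility analyses separately plans bootstrap intervals for between-group differences in mean cost and mean effect.

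**The concern.** The definition, the unit of calculation and the decision rule do not fit together. The definition is an increment between arms, but the unit is one participant, who is randomised to one arm. The same symbol then carries the > €0 rule. The text does not say whether the rule applies to a participant's value, to an arm mean or to the regression coefficient.

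Aim 7 asks which employees the intervention suits best economically, and this section is the only method the article describes for it. An analyst who followed the wording literally could test against zero a quantity that also contains general health level, or improvement that would have occurred without treatment. All participants enter with PSS ≥ 22, so some improvement in every arm is plausible.

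**Working it through.** The section gives no numerical result, so there is no figure to reproduce. The check is algebra followed by an illustration.

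**Inputs from the article.** The definition, unit, regression and rule are as quoted. The total sample is 408 (Sample size calculation), or 408 / 3 = 136 per arm if allocation is equal, which is an assumption.

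**Inputs assumed, because the article gives none.** WTP is €20,000 per QALY. The control arm has mean six-month QALYs of 0.37, of which 0.02 is improvement over the baseline level of 0.35 (utility 0.70 × 0.5 year). Mean costs in the control arm are €3,600 both before and after baseline. The intervention adds €300 in cost and between 0 and 0.02 QALY.

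**Step 1: the coefficient.** For a participant value y_i regressed on a 0/1 treatment indicator by least squares, the coefficient is mean(y | treated) − mean(y | control).

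- With y_i = NB_i = WTP × QALY_i − Cost_i, it equals WTP × ΔQALY − ΔCost, the incremental net benefit (INB).
- Subtracting a constant from y_i, such as the control mean, leaves it unchanged.
- Using change from baseline leaves its expectation unchanged under randomisation.
- If a true between-arm increment were available for every person, regressing it on treatment would give a difference of increments, not the INB. The dependent variable therefore cannot be what the definition says it is.

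**Step 2: expected values by hand, for ΔQALY = 0.01.**

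- True INB: 20,000 × 0.01 − 300 = −€100, not cost-effective.
- Raw net benefit, control: 20,000 × 0.37 − 3,600 = €3,800.
- Raw net benefit, treated: 20,000 × 0.38 − 3,900 = €3,700. Difference: −€100.
- Change from baseline, control: 20,000 × 0.02 − 0 = €400.
- Change from baseline, treated: 20,000 × 0.03 − 300 = €300. Difference: −€100.

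Both coefficients are negative and correct. Both treated-arm means are positive.

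**Step 3: simulation with 400,000 per arm, ΔCost = €300, amounts in €.**

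| ΔQALY | True INB | Coefficient, raw NB | Coefficient, change | Treated mean, raw NB | Treated mean, change |
|---|---|---|---|---|---|
| 0 | −300 | −314 | −301 | +3,500 | +98 |
| 0.005 | −200 | −199 | −192 | +3,601 | +203 |
| 0.01 | −100 | −92 | −101 | +3,699 | +301 |
| 0.02 | +100 | +94 | +99 | +3,899 | +499 |

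The coefficient has the right sign in every row. The treated-arm mean is above zero in every row, including the three where the intervention is not cost-effective. In the −100 row, about 90% of participants in each arm have a raw net benefit above zero.

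**Step 4: a participant value centred on the control mean.** The treated-arm mean is then the INB itself, so a rule read on that mean gives the right answer. A count of individuals does not: in the −100 row, 53% of treated participants are above zero.

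**Step 5: trial-sized samples.** In one simulated trial with 136 per arm (ΔQALY 0.01, ΔCost €300, WTP €20,000), the aggregate INB and the coefficients for raw and control-centred net benefit were all −40.02. The change-score coefficient was −20. Raw and change scores agree in expectation but need not agree in one trial, so the dependent variable should be named.

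**The case against.** The strongest defence is that the section already contains the right analysis. The values are regressed on treatment for the purpose of "to evaluate the cost-effectiveness of the intervention relative to the control condition", and the next sentence states the rule for the intervention, not for a participant. The natural referent of the rule is then the regression result, and step 1 shows that result is correct. Subgroups are handled by interaction terms, which centring the outcome does not alter. The section on cost-effectiveness and cost-utility describes WTP correctly, so the slip here is unlikely to mislead. The analysis is exploratory and the main economic results come from elsewhere.

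All of this stands, and it limits the point. It does not make the text consistent. The rule names the symbol that was just assigned to participants, and the coefficient is never mentioned. An interaction coefficient shows how subgroups differ in INB, but not whether the INB in a given subgroup is above €0, so the rule still needs a defined quantity there.

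A reader might go further and infer three things that the article does not support:

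- **That the plan will reach a wrong verdict.** This follows only if the rule is read on participant values or on an arm mean. The text does not say that it is.
- **That natural recovery could make even the waiting list count as cost-effective.** Suppose every arm gains 0.01 QALY at no cost. Each mean change is 20,000 × 0.01 = +€200, but the planned regression returns 200 − 200 = €0, and the rule read on the coefficient is not met.
- **That change from baseline is the only per-person difference available.** Deviation from the control mean can also be computed, and the article does not mention change from baseline for this analysis.

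**Conclusion.** The paragraph is wrong as written, in three respects. It assigns a between-arm increment to single participants. It attaches the > €0 rule to a symbol with two meanings. It describes WTP × Δ(QALY) as the willingness to pay for one QALY, which is WTP alone.

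The consequence is conditional. Read on the treatment coefficient, the rule gives the right answer. Read on raw or change-from-baseline participant values, or on their arm mean, it can call an intervention cost-effective when its INB is zero or negative. In the illustration the treated-arm mean change was still +€98 with a true INB of −€300. These amounts depend on the assumed WTP, QALYs and costs. The mechanism does not: an arm mean that is not set against control includes what would have happened without treatment.

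This should be fixed, but it is not critical. The regression is exploratory, and the main cost-effectiveness and cost-utility analyses rest on between-group mean differences that this paragraph does not touch.

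**What to change.** Replace the paragraph's definitions and rule with wording to this effect:

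*For each participant, NB_i = WTP × QALY_i − Cost_i, where WTP is the willingness to pay for one additional QALY. NB_i is regressed on separate indicators for the guided and unguided arms, with the waiting list as reference, adjusting for baseline EQ-5D utility and baseline costs. The coefficient of each indicator is the incremental net benefit of that arm. An arm is judged cost-effective at a given WTP when its coefficient exceeds €0, and the coefficient is reported with its uncertainty over a range of WTP values. Effect modification is read from the treatment × modifier coefficients.*

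Two notes:

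- The INB in a subgroup is the arm coefficient plus the interaction coefficient times the modifier value, and any €0 judgement for a subgroup belongs to that sum. The guided versus unguided contrast is the difference between the two arm coefficients.
- The baseline covariates are not needed to remove bias under randomisation. They account for chance imbalance and can improve precision.

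The cost is one reworded paragraph. Table 2 shows the EQ-5D and the cost questionnaire at both baseline (T1) and six months (T3), so no new data are needed and the same regression software serves.
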